# **The Chinese Multi-Center Screening Trial (CHIMUST)**

## **The Prevention of Cervical Cancer Using Self-collection as the Primary Screen**

### **1. Objectives**

The primary objective of the project will be to evaluate the Cobas 4800 Assay and the SeqHPV Assay for the detection of high grade pre-cancer of the uterine cervix in population based screening samples obtained using self-collection.

#### **1.1 Secondary Objectives:**

- 1) To evaluate differences in assay performance using solid (filter paper cards), dry brush, and liquid based specimen transport for the self-collected and physician collected cervico-vaginal specimens.
- 2) To evaluate cytology and genotyping as secondary screens after primary HPV screening using Cobas 4800, and SeqHPV.

### **2. Background and Significance**

There is now significant evidence that molecular testing for (hrHPV) is more sensitive and less specific than cervical cytology for the detection of cervical precancer (CIN3 and AIS) and cancer(1-7). High-risk HPV testing is more reproducible than cytology (8,9) and with appropriate management can reduce the risk of incident cervical cancer within 4-5 years (6) and cervical cancer-related death within 8 years (7). As a consequence of its greater sensitivity for clinically important precancerous lesions, a negative hrHPV test provides a greater reassurance against incident cervical precancer and cancer than cytology (10-12), permitting safe extension of screening intervals (13).

By extension, the high sensitivity of hrHPV testing for high-grade cancer precursors and the declining level of HPV detection in normal women over the age 30 (an accepted surrogate for persistent disease) establishes testing for hrHPV as a more effective primary screen for women over 30 than cervical cytology as is currently practiced. One or two screenings in a woman's lifetime between the ages of 30 and menopause is sufficient to have a significant impact on mortality from cervical cancer (14). This now evident from multiple clinical trials. (6).

One of the advantages to switching from cytology to hrHPV testing is the possibility of using self-collected cervico-vaginal specimens, which avoids the costs and resources necessary to do a clinic-based speculum exam to obtain a cervical specimen. Self-collection and hrHPV testing has been shown to be at least as sensitive for cervical precancer and cancer as high-quality cytology (15).

We have previously demonstrated in a large population based clinical trial, The Shenzhen Cervical Cancer Screening Trial II (SHENCCAST II) that using the PCR based multiplex genotyping assay developed by BGI Shenzhen, Shenzhen, China, for mass spectrometry (MALDI-TOF-MS), a self-collected sample was equal in sensitivity to a physician obtained specimen. (16,17). These findings confirmed similar results using the Roche Linear Array Assay (18), and were supported by the

analysis of the SHENCCAST II samples using the new SeqHPV (BGI Shenzhen, Shenzhen, China)(19).

In order to apply these findings to large scale screening programs, we designed this study to use the FDA and SFDA approved Roche Cobas Assay (Roche Inc., Pleasanton CA, USA) and the new SeqHPV assay based on next generation sequencing developed by BGI Shenzhen to compare the test results from self-collected and direct collected samples and to evaluate variety specimen transportation media for each of the 2 HPV assays.

The Cobas4800 is a qualitative multiplex HPV testing assay. The test utilizes amplification of target DNA by PCR, and nucleic acid hybridization for the detection of 14 high-risk (HR) HPV types. It provides specific genotyping information for HPV types 16 and/or 18, and then pools the results for the other 12 high-risk HPV types. (20,21) Prior studies have consistently demonstrated that self-collected samples perform best when combined with a PCR based assay (16-19,22). Since the Cobas 4800 (Cobas) is both FDA and SFDA approved we feel it is important to trial the assay with self-collected samples.

The SeqHPV test is a high throughput HPV genotyping assay based on multiplex PCR and next generation sequencing. It is configured to detect 14 high risk types of HPV with a current throughput of greater than 6000 samples per day and a patient charge per sample about 1/10 other assays (~ 5 US dollars). These characteristics make it well suited for centralized laboratory processing in high volume screening programs. The assay has been previously validated using SHENCCAST II specimens. (19)

Traditionally cervical swabs have been placed in liquid media for transport. Due to the logistical difficulties such as spillage, flammability, and weight adding to the risks and costs of liquid transport media, solid carriers consisting of chemically treated or untreated filter paper have been investigated for hrHPV testing [23-34]. Solid carriers have been historically used for postnatal screening of congenital disorders [35] and more recently to detect viruses, such as HIV, and tropical diseases [36-40]. These filter paper cards are easy and safe to store and transport. Recently we (Maurer, et.al.) designed and tested a new solid media transport card that was compared to the established iFTA card from GE Healthcare. (41). The new card performed equal to the iFTA card in terms of transfer of HPV DNA and sensitivity/specificity for CIN2+. Functionally the chemistry on the card changes color with placement of the sample, lyses cells and denatures proteins upon contact, making the samples noninfectious. Importantly, the new card (POI Card), did not degrade in high humid environments like the iFTA card and it is considerably cheaper. In addition, in a sub study (Luo et. al.) provides data to suggest the iFTA may be a poorer transport vehicle than the POI card when combined with the Cobas assay. [42] Therefore for this trial we will employ the recently validated POI card, the standard PreservCyt liquid (TCT-Hologic Inc., Bedford, MA, USA). In addition we will collect “dry brush” samples from the very high-risk Inner Mongolia subset. This transport technology is of particular interest for several reasons: 1) it is very inexpensive; 2) the cards require either complex punching technology or considerable manpower upon reaching the laboratory, especially if screening programs hope to achieve high throughput; and 3) the most commonly used transport media (PreservCyt/TCT) are alcohol based and therefore restricted from routine air transport and carry some risk for home use.

For self-collected specimens the well-tested and validated split-sample methodology will be employed by using the card 1st then rinsing the brush with the residual sample in PreservCyt (TCT) transport media. (43,44).

In addition at the time of the physician visit (after the self-collection), the physician will obtain 2 “pseudo self-sample” specimens (prior to placement of a speculum). These 2 samples will be kept as “dry brush samples” by placing them in plastic bags and analyzed  $\leq 7$  days and  $> 6$  wks, respectively. (45)

As mentioned above, the major problem with primary HPV testing is specificity, since most of the women testing positive will have non-neoplastic HPV infections that will spontaneously clear. To address this issue we have previously investigated primary HPV screening with a mRNA assay. (46) In addition we have explored the use of 16/18 genotyping as well as multiple other HPV types for secondary triage after primary screening using both the Cervista assay and MALDI-TOF MS. (47,48) This current trial will provide the opportunity to expand that work applied to self-collection, the Cobas assay (tests for 16 and 18 separately), and SeqHPV with separate gene sequencing for 14 HPV High-risk types.

### **3. Study Design**

#### **3.1 Methods**

This is a multicenter population-based cross-sectional cervical cancer-screening study that will provide screening for 10,000 women who have not been screened for cervical cancer in the past 3 years. The project will be submitted to the Peking University Shenzhen Hospital institutional review board and the IRB of the Cleveland Clinic in Cleveland, Ohio, USA for study approval. In addition the study will be registered with the Chinese Clinic Trial Registry, an international clinical trials registry platform approved by the WHO.

The clinical study consists of 1 self-sampling and 1 direct-sampling on all participants and 2 pseudo-self-sampling on participants in a high risk subset, all the samples will be used for multiple assays followed by referral for colposcopy and biopsy of women with positive test results from self-collection (any one assay), liquid direct collection (any one assay), plus pseudo-self-collection.

- 1) Recruitment of 10,000 patients for screening and participation in the study (Addendum flow chart)
  - Eligibility Criteria: non-pregnant, 30-59 yrs. of age, no screening for at least 3 years, no prior hysterectomy, no prior radiation, and willing to return for positive management if indicated by the primary tests.
  - Exclusion Criteria: Pregnant,  $< 30$  and  $> 59$  yrs of age, screening in the previous 3 years, history of a hysterectomy, pelvic radiation therapy, or not willing to return for positive management if indicated by the primary tests.
- 2) Informed consent

- 3) Demographics
- 4) Patient obtains 1 self-sample placed on the solid media transport card and then the brush (used as a split sample) placed and agitated in PreservCyt Liquid. The card sample will be obtained using the validated “Just for Me”™ kit, which includes a POI brush designed for both self and direct collection, a solid media specimen transport card (POI Card), and an envelope, all bar coded and contained within an outer envelope with language specific and pictorial sampling instructions. The PreservCyt sample will use the same POI brush and the sample will be placed directly into a vial containing 6ml PreservCyt.

- # 1 sample is first rubbed on the POI Card, then the brush agitated in a 6ml PreservCyt (TCT) (the split-sample).

These self-samples transported by card and liquid will be assayed using a) Roche-Cobas 4800 and b) BGI-SeqHPV test.

- 5) At ALL sites a physician will then place a vaginal speculum so as to directly-collect an endo-cervical sample from each of the participants. The sample is placed in 20ml ThinPrep® PreservCyt® (TCT) Solution (Hologic); ONLY in Inner Mongolia, prior to placement of the vaginal speculum, the physicians will obtain 2 “pseudo self-samples” which are allowed to dry, then placed into plastic bags for testing at ≤7days and >6wks respectively using a) Roche-Cobas 4800 and b) BGI-SeqHPV test.

The direct samples will be assayed using a) Roche –Cobas and b) BGI-SeqHPV.

Cytology using the Hologic I2 imager systems (computer assisted cytology) will used for future research not for patient care in the current study. The primary goal will be to explore secondary triage for the non-16/18, HPV positive women.

**POI Card Management Protocol** – Each card will be manually punched 4 times and placed in a single well in a 96-well plate. Then they are all washed once using 100 microliters sterile water. The water is carefully removed with a sterile fine-tip pipette. The DNA elution is performed in 50 microliters of sterile water at 56°C for 30 min immediately followed by 95°C for 15 min. in a heating block. The 96-well plate containing DNA elution and pieces of card are centrifuged at 4000 rpm for 3 min and the eluted DNA is transferred into a new 96-well plate. (Any required storage will be at -80°C for further use). When performing the assays 5ul of DNA will be used in each well of the 96 well plates for PCR for SeqHPV. 10ul will be used for a nested case control study using Cobas. (It should be noted that this is the standard volume used for SeqHPV, and it has been thoroughly tested and demonstrated to be optimal with > 99% adequate specimens. It was determined in our prior study that 10ul optimized the Cobas Assay when using the POI card.)

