#### *Statistical Methods*

The primary endpoints of our study will be the sensitivity and specificity of the hrHPV tests for cervical intraepithelial neoplasia (CIN) 3 or cancer (CIN 3+). The secondary endpoints will be the sensitivity and specificity of the hrHPV tests for CIN 2+.

Our estimates of the difference in sensitivity for CIN 3+ and specificity for CIN 3+ that may be detected are based on the prevalence of hrHPV and prevalence of CIN 3+ (the primary endpoint) or CIN 2+ (the secondary endpoint) in the population studied. Our estimates of the prevalence of hrHPV and CIN 3+ are likely more accurate than in many studies as we can use the data from SHENCCAST II (17) as a guide. In SHENCCAST II (17), we screened populations similar to four of our study sites; and our fifth site (Inner Mongolia) has known hrHPV rates and resulting pre-invasive/invasive cervical cancer considerably higher than any sites in SHENCCAST II. Adding the site in Inner Mongolia should compensate for the age difference of 25-59 years (SHENCCAST II) vs. 30-59 years for the current trial (CHIMUST).

As in SHENCCAST II, sensitivities and specificities will be calculated for each hrHPV tests. Logistic regression analysis will be used to generate odds ratios and 95 % CI for factors that may be associated with test results by sampling device.

Sample size calculations to compare the sensitivity and specificity of hrHPV tests are based on the prevalence of hrHPV and the prevalence of the endpoint (CIN 3+ or CIN 2+) in the population. In SHENCCAST II, the prevalence of hrHPV measured in vaginal self-collected or endocervical practitioner-collected samples and tested for hrHPV by MALDI-TOF or Cervista assays was between 11.1% and 14.8%. The prevalence of the primary endpoint of CIN 3+ in SHENCCAST II

was 1.6% (141/8,556) while that of the secondary endpoint of CIN 2+ was 2.7% (227/8,556). The major results from SHENCCAST II are reproduced in Table 1 below. The SeqHPV assay being used in this trial, was trained and tested on SHENCCAST II specimens and showed results similar to MALDI-TOF. (19)

**Table 1: Comparison of the sensitivity and specificity for  $\geq$ CIN 3 of vaginal self-collected and physician collected specimens (endocervical) assayed for HR-HPV by Cervista and MALDI-TOF.**

(95% confidence intervals and the actual patient numbers are in parentheses).

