McNemars p-values for the comparison of the sensitivity of self-collected MALDI-TOF to physician collected Cervista is 1.0. McNemars p-value for the comparison for the specificities is  $p < 0.0001$

| SPECIMEN/HR-HPV TEST        | SENSITIVITY FOR <math>\geq</math>CIN 3 (%) (C.I.)(n) | SPECIFICITY FOR <math>\geq</math>CIN 3 (%) (C.I.)(n) |
|------------------------------------|-------------------------------------------------------------|-------------------------------------------------------------|
| Vaginal self-collected / Cervista  | 70.9% (62.7-78.3) (100/141)                          | 86.1% (85.3-86.8) (7248/8415)                        |
| Endocervical / Cervista            | 95.0% (90.0-98.0) (134/141)                          | 90.3% (89.6-90.9) (7598/8415)                        |
| Vaginal self-collected / MALDI-TOF | 94.3% (89.1-97.5) (133/141)                          | 87.5% (86.8-88.2) (7370/8415)                        |
| Endocervical / MALDI-TOF           | 94.3% (89.1-97.5) (133/141)                          | 89.4% (88.7-90.0) (7526/8415)                        |

The 95% CI for the sensitivity of hrHPV in Table 1 spans about 8%, suggesting that, with a study involving 10,000 women with prevalence of hrHPV of 11.1 to 14.8% and prevalence of CIN 3+ of 1.6%, we can reliably detect a difference in sensitivity of about 8%. The 95% CI for the specificity of hrHPV in Table 1 spans only about 1.3% suggesting that we can reliably detect differences in specificity of the hrHPV test greater than 1.3%. As we have paired specimens, the difference in sensitivity for CIN 3+ that can reliably be detected is closer to 7% i.e. 94.3% (133/141) vs. 87.2% (123/141) rather than 8%.

*Primary Objective: Evaluation of the Cobas 4800 Assay, and the SeqHPV Assay for the detection of high grade pre-cancer of the uterine cervix, in population based screening samples obtained using self-collection.*

To evaluate the comparative sensitivities and specificities of the hrHPV platforms, the sensitivity and specificity of each test will be calculated using biopsy showing CIN 3+ (primary endpoint) or CIN 2+ (secondary endpoint) as the gold standards.

*Secondary objective 1: To evaluate differences in assay performance using solid (filter paper cards), dry brush, and liquid based specimen transport for the self-collected and physician collected cervico-vaginal specimens.*

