To determine which kind of sample collection media is a suitable medium for collecting and storing vaginal self-samples relative to the assay used we will calculate sensitivities for detecting CIN2+

and CIN3+ and the number of insufficient samples for hrHPV testing of the different sample collection transport systems.

*Secondary objective 2: To evaluate cytology and genotyping as secondary screens after primary hrHPV screening using Cobas and SeqHPV.*

The focus will be to explore practical algorithms that will maximize specificity for CIN 3+ with minimal loss in sensitivity for CIN 3+. Differences in sensitivity and specificity for CIN 3+ will be compared with McNemar's test when there are paired results and Chi-Square when there are independent groups. Cytology will be analysed as a triage technology with a special focus on the non-HPV 16/18 positive population. For the genotyping analysis the available types (14 HPV types) will be used from SeqHPV. Types 16/18 will be used from SeqHPV and Cobas.

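### Secondary objective 1 compares collection-plus-transport systems, not media alone, and the full-sample 7-point precision does not carry over to the one-site dry-brush comparison

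*Protocol*

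**What the plan says.** The Statistical Methods section, under secondary objective 1, aims to find "a suitable medium for collecting and storing vaginal self-samples", relative to the assay used. It will do so by calculating sensitivities for CIN 2+ and CIN 3+ and counting insufficient samples for each transport system. The specimens are defined in sections 2 and 3.1:

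- **Card and self-collected liquid.** Every woman takes one self-sample. The brush is rubbed on the card first, "then rinsing the brush with the residual sample in PreservCyt (TCT) transport media" (6 ml).
- **Dry brush.** "ONLY in Inner Mongolia, prior to placement of the vaginal speculum, the physicians will obtain 2" pseudo self-samples. Section 2 places them after the self-collection. Sample A is tested at 7 days or less. Sample B is a nested analysis after more than 6 weeks.
- **Physician liquid.** A direct endocervical sample from every participant, placed in 20 ml PreservCyt.

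On precision, the protocol refers to what can be achieved "with a study involving 10,000 women with prevalence of hrHPV of 11.1 to 14.8% and prevalence of CIN 3+ of 1.6" percent. It adds that, because specimens are paired, "the difference in sensitivity for CIN 3+ that can reliably be detected is closer to 7" percent, illustrated as 133/141 against 123/141. It gives no enrolment figure and no precision figure for Inner Mongolia alone.

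**The concern.** The question asked is about self-samples, but one of the three media is never used for a self-sample. A dry-brush result differs from a card or self-collected liquid result in who took it, when it was taken and which brush was used, as well as in the medium. Card and self-collected liquid come from the same brush in a fixed order, so that contrast mixes medium with order.

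The protocol calls the Inner Mongolia subset very high-risk and reports a 22% HPV infection rate there. If dry-brush sensitivity from that site is tabulated beside five-site card or liquid sensitivity, differences between populations enter as well. Nothing in the text on secondary objective 1 prevents this.

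The stakes are practical. Section 2 describes dry brush as of particular interest because it is cheap and avoids alcohol-based media in transport and at home. A finding of no difference at one site could be read as support for dry-brush self-collection when the design has no such sample and few cases with which to detect a loss of sensitivity.

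**Working it through.** **1. What each contrast isolates**

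| Contrast | Differs in, besides medium |
|---|---|
| Card vs self-collected liquid | order (card always first) |
| Dry brush A vs card or self-collected liquid | collector, order, brush; also site if not restricted to Inner Mongolia |
| Physician liquid vs self-collected card or liquid | collector, anatomical site (endocervical) |
| Dry brush A vs B | storage time is the intended difference; sampling order too if allocation follows it |

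None of the first three isolates the medium. A against B holds collector, site and medium constant, but the protocol does not say how the two brushes are allocated to A and B.

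**2. The protocol's own figure**

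The difference is (133 − 123)/141 = 10/141 = 7.1 points. The exact 95% CI for 133/141 is 89.1 to 97.5%, a width of 8.4 points, which matches the stated span of about 8.

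The protocol gives no alpha, power or discordance, so I assumed two-sided 0.05 and 80% power. Let n be the number of CIN 3+ cases, c the reverse discordance (proportion of cases positive only on the worse system) and d the difference in sensitivity. The other discordant cell is then c + d. Power is the rejection probability of McNemar's test averaged over the number of discordant pairs, Binomial(n, 2c + d).

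With n = 141 and c = 1.4% (2/141), the detectable d is 7.1 points (uncorrected McNemar) or 7.8 (exact). With n = 160 (10,000 × 1.6%), it is 6.4 or 7.1. About 7 points is therefore attainable for the full sample if reverse discordance is low.

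**3. Cases at one site**

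Inner Mongolia enrolment is assumed to be 10,000/5 = 2,000.

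- At the reference-trial prevalence: 2,000 × 141/8,556 = 33 cases.
- If CIN 3+ scales with hrHPV, using 22% against the midpoint of 11.1% and 14.8% (12.95%): 33 × 22/12.95 = 56 cases.

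**4. Detectable paired difference at 80% power (points, uncorrected to exact McNemar)**

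| Cases | c = 0 | c = 1.4% | c = 3% |
|---|---|---|---|
| 33 | 16.1 to 23.0 | 21.0 to 25.5 | 24.9 to 28.4 |
| 56 | 9.7 to 13.8 | 14.0 to 16.3 | 16.9 to 18.8 |

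**5. Power for a 7.1-point difference, c = 1.4 to 3%**

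- 33 cases: 4 to 5% (exact), 18 to 20% (uncorrected).
- 56 cases: 18 to 20% (exact), 29 to 40% (uncorrected).

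Even at c = 0 with 56 cases, power is 20% (exact) or 57% (uncorrected).

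**6. What 7.1 points would need**

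By the exact test at 80% power, 111 cases (c = 0) or 146 (c = 1%) are needed. In 2,000 women that is a CIN 3+ prevalence of 111/2,000 = 5.6% or 146/2,000 = 7.3%, against 1.6% in the reference trial.

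**The case against.** The design choices are declared. The dry brushes are openly called pseudo self-samples and limited to one site, and card-first is presented as an established split-sample method. They limit interpretation and are not contradictions. That stands. Several stronger readings are tempting, and the protocol does not support them.

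- **That all liquid is card residue.** Only the self-collected liquid is. The 20 ml physician liquid is a separate sample, though its different collector and anatomical site mean that it does not isolate the medium either.
- **That site unavoidably confounds dry brush.** Inner Mongolia women supply every specimen type, so a within-woman comparison removes site. Collector and order remain, as do few cases and limited generalisability.
- **That the protocol claims 7 points for dry brush.** It does not; the figure is tied to 10,000 women. The gap is that no other figure is offered.
- **That chi-square is planned for dry brush.** The sentence on McNemar and chi-square stands under secondary objective 2 and prescribes McNemar for paired results. Secondary objective 1 names no test.
- **That Table 1 shows a large collector effect here.** The 70.9% against 95.0% gap is for Cervista, which this trial does not use, and compares vaginal with endocervical samples. MALDI-TOF in the same table shows 94.3% for both, and the protocol says SeqHPV gave results similar to MALDI-TOF. Table 1 says nothing about site or sampling order.

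The precision figures also rest on an enrolment and a prevalence that the protocol does not state, and Sample B, being nested, may have fewer cases than Sample A. Finally, nothing says that A is always taken first; the point is only that allocation is unspecified. One could leave the analysis set and test to the SAP, but the SAP cannot supply a self-collected dry brush, so the objective's wording still needs correcting.

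**Conclusion.** The point holds in limited form. As worded, secondary objective 1 promises a conclusion about media for self-samples that these specimens cannot give. They can compare collection-plus-transport systems, and for dry brush only as taken by a physician at one site. Site confounding is avoidable and arises only if one-site and five-site results are set side by side.

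The full-sample precision does not carry over. With 33 to 56 cases, the dry-brush comparison can detect about 14 to 28 points at 1.4 to 3% reverse discordance, and about 10 to 23 near zero. This assumes 2,000 women at the site, CIN 3+ prevalence between the reference-trial rate and that rate scaled to 22% hrHPV, two-sided 0.05 and 80% power. These numbers show the scale of the loss. They should not be entered in the protocol as fact while enrolment at the site is unstated. The primary objective is unaffected.

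**What to change.** 1. Analyse every dry-brush contrast within Inner Mongolia women who have both results, with McNemar's test and a paired confidence interval, and do not compare dry brush with pooled five-site estimates.
2. State that the 7-point figure applies to full-sample comparisons only. Give the dry-brush precision from the planned Inner Mongolia enrolment, with the assumed prevalence and discordance, and treat the nested Sample B separately.
3. Randomise by pre-printed barcode which of the two dry brushes becomes Sample A and which Sample B, so that storage time is not tied to sampling order.
4. Word conclusions as physician-taken dry brush and residual self-collected liquid after card, with no claim about medium alone or about dry-brush self-collection.

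The cost is wording, one short calculation and a random label order at one site. The dry-brush conclusion becomes narrower.

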### Sample applications:

- 1 Self-collection -----to ❶ POI Card ---- then Split Sample into ❷ PreservCyt (6ml)
- 2 Physician pseudo self-collections – (Inner-Mongolia site only) ❸ Dry Brushes stored Dry for analysis, **Sample A**  $\leq 7$  days; **Sample B** nested analysis  $> 6$  wks
- 1 Physician Direct endocervical collection -----to ❹ PreservCyt (20ml)

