### Assay:

- From the ❶ POI Card -----All SeqHPV (5ul HPV DNA); *nested* Cobas (10ul HPV DNA)
- From the ❷ PreservCyt (6ml) -----Cobas (1ml), SeqHPV(1ml)
- From the ❸ Sample A (reconstituted) ---- Cobas (1ml), SeqHPV (1ml)
- From the ❸ Sample B (reconstituted) -----*nested* Cobas (1ml), SeqHPV (1ml)
- From the ❹ PreservCyt(20ml)-----Cobas (1ml), SeqHPV(1ml), and Cytology.

- 6) Patients testing hrHPV positive from any of ❶ - to ❹ will be recalled for colposcopy using the POI protocol of directed and/or random biopsies plus ECC (49).
- 7) Patient management will be determined based on biopsy results and according to current standards at the Peking University Shenzhen Hospital.

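### The protocol gives no rule for which of the two dry brushes is tested at ≤7 days and which at >6 weeks, so a difference between them could not be attributed to storage alone

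*Protocol*

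**What the plan says.** Item 5 of Section 3.1 says that, in Inner Mongolia only, "prior to placement of the vaginal speculum, the physicians will obtain 2" pseudo self-samples. These are "allowed to dry, then placed into plastic bags for testing at ≤7days and >6wks respectively", with Cobas and SeqHPV. Section 2 gives the same pairing of brushes and test times ("by placing them in plastic bags and analyzed" at the two ages) and adds that they follow the woman's own self-collection.

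The sample list in Section 3.1 names the brushes by test age: "Dry Brushes stored Dry for analysis, Sample A" is the one for ≤7 days, and Sample B, marked "nested analysis", is the one for >6 weeks. The assay list sends both to the same two assays.

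The purpose comes from secondary objective 1 (Section 1.1): "To evaluate differences in assay performance using solid (filter paper cards), dry brush, and liquid based specimen transport". Under Statistical Methods this is expanded to finding a "suitable medium for collecting and storing vaginal self-samples relative to the assay used". The outputs named there are sensitivity for CIN2+ and CIN3+ and the count of insufficient samples, by transport system. No test of A against B is stated.

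**The concern.** Both brushes come from the same woman, the same collector and the same dry medium, and go to the same assays. Age at testing is the only planned difference, so a reader will take B against A as evidence on how well a dry brush keeps. That holds only if the brushes are otherwise exchangeable. They are taken one after the other, and a later pass may collect fewer cells, or more.

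If order goes with test age, poorer collection on the later brush would look like loss of DNA in the bag and would count against a transport method that Section 2 favours for its low cost. If the later brush happened to collect better, real storage loss would be hidden. Allocation happens at the bedside, so this is a matter for the protocol and cannot be left to an analysis plan.

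**Working it through.** The protocol gives no sample size, power or effect figure for the two-age comparison, so there is no figure to reproduce. The check is whether the storage effect can be identified.

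**Model.** Let S be the change in detection from late testing, and W the change from being the second brush rather than the first. Both are on the scale of the paired difference B − A.

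- A always first, B always second: B − A = S + W. With columns for intercept, late testing and second brush, the rows are (1,0,0) and (1,1,1). The matrix has rank 2 for 3 columns, so S and W are aliased.
- Staff choose, with A first in an unrecorded share q of women: the expected difference is q(S + W) + (1 − q)(S − W) = S + (2q − 1)W. The bias lies between −W and +W. It vanishes only at q = 0.5, and q is unknown.
- Counterbalanced and recorded: the rows are (1,0,0), (1,1,1), (1,0,1) and (1,1,0), with rank 3 of 3. The mean of the two sequence groups is [(S + W) + (S − W)]/2 = S. Half their difference is W.

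**Illustration on HPV positivity.** The documents give 10,000 women over five sites and a reported HPV rate of 22% in Inner Mongolia. Assumed: 1,000, 2,000 (one fifth) or 3,000 women at that site; B read in all positives; no storage effect; A always first; 3% chance discordance in each direction; and a second-brush loss of 2% or 5%.

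| Women | Positives (× 0.22) | Loss 5%: discordant pairs, apparent drop, exact McNemar p | Loss 2%: same |
|---|---|---|---|
| 1,000 | 220 | 18 v 7, 11/220 = 5.0%, p = 0.043 | 11 v 7, 4/220 = 1.8%, p = 0.48 |
| 2,000 | 440 | 35 v 13, 22/440 = 5.0%, p = 0.002 | 22 v 13, 9/440 = 2.0%, p = 0.18 |
| 3,000 | 660 | 53 v 20, 33/660 = 5.0%, p = 0.0001 | 33 v 20, 13/660 = 2.0%, p = 0.10 |

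The apparent storage drop equals the assumed order loss, up to rounding of counts, at every sample size. Only the p-value changes. With counterbalanced order the expected drop is 0.

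**On the measure the protocol names.** At the prevalences quoted from the earlier Shenzhen trial (1.6% CIN3+, 2.7% CIN2+), 2,000 women give 32 CIN3+ and 54 CIN2+. A 5% order loss is then 0.05 × 32 = 1.6 and 0.05 × 54 = 2.7 women. Doubling the prevalence, as an assumption for a higher-risk site, gives 3.2 and 5.4. With all discordance in one direction, exact McNemar gives 2 × 0.5⁵ = 0.0625 for 5-0 and 2 × 0.5⁶ = 0.031 for 6-0. On expected counts, an order effect of this size would not reach significance on the planned measure.

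**The case against.** The strongest reply is that the protocol never calls either brush first or second and defines A and B by test age alone. *Respectively* may mean only that one brush goes to each age. A reader might infer that the first brush always goes to ≤7 days, so that order and storage coincide in every woman. That is the natural reading of an ordered pair labelled A then B, but the documents do not state it. This part of the reply stands: complete confounding follows if the written order is followed, and is not a fact of the text. It does not remove the point, because free choice leaves order uncontrolled and unrecorded.

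It can also be said that labelling two bags is a bench detail, and that the flow chart, which could not be read in the copy reviewed, may cover it. If the chart gives an allocation rule, the point falls. The written steps give none.

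Third, storage time is not a named objective, no A-against-B test is planned, B is a nested analysis, and Sample A carries the comparison of dry brush with card and liquid. All of this is correct and limits the consequence. It does not make the comparison empty: the protocol speaks of storing as well as collecting, and B differs from A by design only in age at testing.

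**Conclusion.** The point holds as a minor one. The protocol ties two successive brushes to two test ages without randomising, alternating or recording which is which. A difference between the >6-week and ≤7-day results would therefore carry an unknown part of any order effect, up to all of it.

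Two stronger conclusions are tempting and not supported. One is that the storage part of secondary objective 1 cannot be answered at all. The documents plan no formal storage contrast, and it is the attribution of a difference to storage that is insecure. The other is a stated rate of false storage findings. Any such rate rests on an assumed site size, discordance and order effect. It also uses HPV positivity in all positives, whereas the protocol plans CIN2+ and CIN3+ sensitivity and a nested subset for B. The p-values in the table are illustrations of this kind only.

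The primary objective and the comparison of dry brush (Sample A) with card or liquid are unaffected.

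**What to change.** In Section 2, Section 3.1 item 5 and the sample list, replace the *respectively* assignment with an allocation rule. For example: the two brushes are numbered in order of collection; a pre-printed label list assigns brush 1 to Sample A in half of the women and to Sample B in the other half, at random or by parity of the study ID; the position of each brush is recorded.

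Under secondary objective 1, add that A and B are compared only in women with both results, since B is nested, with brush position as a factor (equivalently, by averaging the two sequence groups).

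The cost is a label list and one extra recorded item. No further sample, test or visit is needed. If brushes have already been collected without a record of order, the A-B difference should be reported as storage and collection order combined.
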